### Conclusion

This study will determine if mobile app technology can be used to replace in-person follow-up care after ambulatory surgery. Such replacement may have multiple secondary ramifications including cost-effectiveness and patient satisfaction.

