**Results:**

A sample of 72 (36 patients per group) will provide an E-test for count data with a power of 95% (*P*=.05) to detect a difference of 1 visit between groups, assuming a 10% drop out rate. Count variables will be analyzed using Poisson regression. Categorical variables will be tested using a chi-square test. Cost-effectiveness will be analyzed using net benefit regression. Outcomes will be assessed over the first 30 days following surgery.

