### Research Question

In postoperative ambulatory breast reconstruction patients at WCH, can we avert in-person follow-up care through the use of a mobile app compared to conventional, in-person follow-up care in the first 30 days following surgery?

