## Methods

### Design Overview

This will be a pragmatic, single-center, open, controlled, 2-arm parallel-group superiority randomized trial comparing mobile app and in-person follow-up care over the first 30 days following surgery. Permutated-block randomization will be conducted by blocks of 4-6 using the program ralloc in Stata statistical software [20].

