### Primary Outcome

The total number of physician visits (including specialist, family physician, and emergency department) related to the surgery. These data will be captured at 4 weeks after surgery.

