### Secondary Outcomes

The total number of health care telephone calls and emails (including specialist, family physician, and emergency department) related to the surgery will be captured at 4 weeks after surgery.

We will also record and report all complications occurring within the 30-day period. This was chosen based on literature surrounding postoperative complications in the first 30 days [21]. This will be captured at 4 weeks after surgery. The complication rate within this patient population is 4%, with 1% rate of reoperation. The most common complications are superficial skin infections managed with a short course of oral antibiotics. In the pilot study, all (1/30) superficial skin infections were picked up by the mobile phone app and antibiotic prescriptions were called in to the patient’s local pharmacy [6]. Rare non-serious complications include seromas and wound dehiscence. All wound dehiscence (1/30) were picked up by the app in the pilot study. These both warrant a trial of conservative (watch-and-wait) therapy. After failed conservative therapy, seroma may be drained via ultrasound guided needle aspiration. Wound dehiscence may require surgical management under local anesthetic in the clinic or, if more involved, under regional anesthetic in the operating room. Rare and potentially serious complications include hematomas. If a hematoma is small and non-expanding, it can be managed conservatively (watch-and-wait). If it is larger and expanding, it may require urgent (<24 hours) evacuation in the operating room. This type of urgent situation presents to the emergency department, not to a clinic visit.

There is no potential for clinical compromise in the telemedicine group. If anything, superficial skin infections may be identified and treated earlier. Any study participant can schedule a face-to-face postoperative visit with the surgeon at any time; however it is anticipated that the mobile phone follow-up care will eliminate the need for one or more clinic visits. Devices may be returned to the clinic in-person or by standard mail.

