### Poisson Regression

We will use person-level Poisson regression to determine if there is a difference in the number of visits attended between patients in the mobile app and in-person follow-up arm.

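### The Conclusion says the trial will determine whether the app can replace in-person follow-up, but the design can show only fewer visits and says little about complications

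*Protocol article*

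**What the plan says.** The Conclusion announces: "This study will determine if mobile app technology can be used to replace in-person follow-up care after ambulatory surgery".

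The rest of the article is narrower:

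- **Research Question:** "In postoperative ambulatory breast reconstruction patients at WCH, can we avert in-person follow-up care", with the app compared to conventional follow-up over 30 days.
- **Design Overview:** a "2-arm parallel-group superiority randomized trial comparing mobile app and in-person follow-up care over the first 30 days following surgery". No non-inferiority or equivalence hypothesis appears anywhere.
- **Primary Outcome:** "The total number of physician visits (including specialist, family physician, and emergency department) related to the surgery".
- **Poisson Regression:** the aim is to "determine if there is a difference in the number of visits attended between patients in the mobile app and in-person follow-up arm".
- **Sample Size:** two visits against one, 32 per arm, raised to 36 for 10% dropout.
- **Intervention:** the app arm has no planned in-person visits at 1 and 4 weeks; photos, pain scores and QoR-9 take their place.

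On complications, the Secondary Outcomes section says "The complication rate within this patient population is 4%, with 1% rate of reoperation". The comparison is covered by one sentence in the abstract's Results: "Categorical variables will be tested using a chi-square test". Complication rate also serves as the effect in the net benefit regression. No margin, interval criterion or power is given for it. The Secondary Outcomes section denies that the app arm can be clinically compromised, while the Risks section accepts that mobile follow-up may affect when a complication is diagnosed. The three items under Limitations do not include imprecision on complications.

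**The concern.** A claim that one form of follow-up can replace another needs two legs: fewer visits, and complications not materially worse when planned visits are dropped. The trial is built for the first leg only. That leg is also partly a product of the allocation, because the app arm's planned visits are taken away by design, so a lower visit count alone says little about whether replacement is acceptable.

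The second leg rests on a test of difference with very few events. The likely report is fewer visits and no significant difference in complications. Set beside the Conclusion as worded, a reader could take that pair as support for replacement when the data could not have shown a large excess of complications.

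**Working it through.** **1. The plan's own figure.** Inputs from Sample Size: mean visits 2 and 1, 32 per arm, 95% power, significance level 0.05 with sidedness not stated. Exact E-test power for two Poisson means:

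- One-sided 0.05: 95.2% at 32 per arm (94.7% at 31), so the stated 32 is reproduced.
- Two-sided 0.05: 91.1% at 32 and 93.9% at 36.
- Dropout: 32 / 0.90 = 35.6, rounded up to 36.

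The size is therefore set by visits alone.

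**2. Expected complications per arm** (n × rate).

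- At 4%: 32 × 0.04 = 1.28; 36 × 0.04 = 1.44.
- At the roughly 5% given in the Introduction: 1.6 and 1.8.
- Chance of no complication in a given arm at 4%: 0.96^32 = 27%; 0.96^36 = 23%.

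**3. Power of the chi-square test.** Sum Bin(a; n, p_app) × Bin(b; n, 0.04) over all pairs (a, b) for which the uncorrected test gives p ≤ 0.05. The app-arm rates are assumed; Fisher's exact test is shown for comparison.

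| App rate (control 4%) | Chi-square, n=32 | Chi-square, n=36 | Fisher, n=32 | Fisher, n=36 |
|---|---|---|---|---|
| 4% | 2.2% | 2.7% | 0.1% | 0.1% |
| 8% | 8.6% | 10.2% | 1.2% | 1.8% |
| 12% | 22.1% | 25.4% | 6.3% | 8.7% |
| 16% | 38.9% | 43.7% | 17.1% | 22.4% |

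The first row shows that the chi-square approximation is itself poor at these counts: its true error rate is about half the nominal 5%.

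**4. What would reach significance.** At 32 per arm, with one control event:

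- 5 v 1: 64 × (5×31 − 1×27)² / (6 × 58 × 32 × 32) = 2.94, p = 0.086.
- 6 v 1: 64 × (6×31 − 1×26)² / (7 × 57 × 32 × 32) = 4.01, p < 0.05.

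So the app arm would need 6 of 32 (19%) against 1 of 32 (3%). At 36 per arm it would also need 6 (17%).

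**5. Interval for the risk difference.** Newcombe upper limit = d + √[(u_app − p_app)² + (p_con − l_con)²], with Wilson limits l and u.

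- 1 v 1 at n=32: Wilson limits 0.55% and 15.74%, so √(12.62² + 2.57²) = 12.9 points either side.
- 1 v 1 at n=36: Wilson limits 0.49% and 14.17%, so √(11.39² + 2.29²) = 11.6 points either side.
- 0 v 0: ±10.7 (n=32) and ±9.6 (n=36).
- 2 v 1: −10.3 to +17.3 (n=32) and −9.3 to +15.6 (n=36).

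**The case against.** The strongest reply is that the operative plan is coherent. Research question, primary outcome, sample size and analysis all concern averted visits, and only one closing sentence goes further. That sentence poses an open question, and low power for a rare secondary outcome is normal in a small trial. The effect measure for complications is often left to the analysis plan. This stands as far as it limits the point to the Conclusion and the reporting of complications; the primary comparison is not affected. But no analysis plan can draw precision from 72 patients, and the one comparison the article does name for complications is a p-value.

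Three stronger readings are tempting, and the article does not support them:

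- **A non-significant chi-square will be taken as proof of safety.** No section says so. The fair criticism is that nothing prevents that reading.
- **The app will be extended to other surgery on the strength of that test.** The Knowledge Translation Plan makes dissemination depend on cost-effectiveness, which comes from the net benefit regression with confidence intervals and an acceptability curve. That analysis does rest on the same few complications.
- **The app arm loses physical examination altogether.** Warning signs lead to an in-person visit, and any participant may book one at any time. Only the planned visits go.

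The population wording is a minor matter. The abstract's Objective and the Conclusion speak of ambulatory surgery, but the abstract's Methods name breast reconstruction and Limitations discusses generalizability.

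**Conclusion.** The point holds as a mismatch between the stated conclusion and what the design can deliver. The trial can determine whether visits fall. It cannot determine whether replacement is safe: with about 1.3 to 1.4 complications expected per arm, roughly 90% of trials would show no significant difference if the app doubled the rate, and 75-78% if it tripled it.

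These figures assume the article's 4% in the control arm, 32 to 36 analysed per arm and an uncorrected chi-square. At 5% the expected count is still below two per arm.

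The imprecision should not be overstated. A reader might infer that even identical results could never exclude a quadrupling, that is, 12 points above 4%. That is so for 1 v 1 at 32 per arm (upper limit 12.9). It is not so for 1 v 1 at 36 (11.6), nor for 0 v 0 at either size (10.7 and 9.6).

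The wording and the complication analysis should be changed; the primary design need not be.

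**What to change.** 1. For complications, report the app-minus-control risk difference with a 95% score interval (Newcombe or Miettinen-Nurminen) in place of the chi-square p-value.
2. Reword the Conclusion to say that the trial determines whether the app reduces physician visits in the first 30 days after ambulatory breast reconstruction. Align the abstract's Objective with the Research Question at the same time.
3. Add to Limitations that the trial cannot establish comparable complication risk, and that a non-significant difference will not be read as such. Require any statement about replacement to quote the upper limit of the interval.

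The cost is some rewording, one interval calculation and a less favourable stated conclusion. No extra patients are needed. Turning this into a non-inferiority trial is not proposed: with an assumed 5-point margin, 4% in both arms, one-sided 0.025 and 80% power, it would take about 242 per arm before dropout.

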## Appendix

Multimedia Appendix 1 Post-pilot satisfaction survey capturing patient satisfaction with care and information provided for all patients, to be completed by all patients at week four.

Multimedia Appendix 2 QoR9 and Pain VAS.

Multimedia Appendix 3 Telephone questionnaire capturing email, telephone and in-person encounters and postoperative complications. All patients will complete this at week four.

Multimedia Appendix 4 Telephone questionnaire capturing patient costs, to be completed by all patients at week two and week four.

Multimedia Appendix 5 CIHR reviewer comments.

## Abbreviations

ASA: American Society for Anesthesiologists
BMI: body mass index
CEAC: cost-effectiveness acceptability curve
INB: incremental net benefit
OHIP: Ontario Health Insurance Plan
QoR: quality of recovery
QoR-9: Quality of Recovery-9
QoR-40: Quality of Recovery-40
REB: Research Ethics Board
VAS: visual analog scale
WCH: Women’s College Hospital
WTP: willingness-to-pay
